### Intervention

Each group will receive a different version of the e- and m-health intervention MyPlan 2.0. MyPlan 2.0 is based upon a previous e-health intervention, called ‘MyPlan 1.0’, which was systematically developed using the intervention mapping protocol [41]. MyPlan 1.0 is a web-based intervention to promote PA and fruit and vegetable intake in the general population, and has been tested in general practice. The programme has shown to be effective in improving healthy behaviour [42–44]. However, high attrition rates were observed and researchers experienced problems with the implementation by general practitioners [42–44]. Therefore, the programme has been further developed into MyPlan 2.0, which participants can use autonomously at home. In order to increase engagement, different adaptations were made based on quantitative and qualitative research [24, 26, 45–47]. MyPlan 2.0 consists of a website (www.mijnactieplan.be/meerbewegen) as well as a mobile application (app). It aims to increase PA and decrease SB in the general adult population (MyPlan 2.0 is also used for another independent study in our research group, which focusses on adults with diabetes mellitus type 2 [48]). The website consists of five weekly sessions, whereas the app offers daily support. Similar to MyPlan 1.0, MyPlan 2.0 is based on self-regulation theory [49, 50] and includes various self-regulation-based behaviour-change techniques [28, 51] in order to bridge the intention-behaviour gap [27, 52, 53]. In both the website and the app, the techniques can easily be removed or added in order to create the different research conditions.

Before the start of the intervention, participants choose which behaviour they want to improve. Participants are free to select either PA or SB. The structure of MyPlan 2.0 is the same for both PA and SB. After behaviour selection, the allocation to one of the research groups takes place. After being allocated into a research group, users will receive different website links to the corresponding interventions.

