The participants will be randomly allocated to eight equal groups (60 participants within one group). The randomisation will be done by the author of this study. Before recruitment of participants, blocked randomisation will be used to form an allocation list for the eight different groups. A computer random number generator (http://www.randomization.com) [59] with a block size of 40 will be used to assign the group numbers in random order within each block. The allocation list will be concealed for the researcher during the recruitment of participants. Each time a participant completes a pre-test measurement (at the library, city hall, shopping mall or at home; see Fig. 4) an automatic email will be sent to the researcher. After receiving this email, the participant will be allocated to the next number on the allocation list and will consequently be assigned to a group. By doing this, the allocation will be concealed until participants are enrolled and assigned to the intervention [60]. After assignment, the researcher will not be blind for the allocated intervention: the researcher will send participants different website links to their corresponding intervention. The participants on the other hand will not be aware of the different conditions of the study: they will only receive one website link (corresponding with their intervention).

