### Data collection procedures

The flowchart of the data collection procedure can be found in Fig. 4. Data collection started in March 2018 and is aimed to finish in April 2019. Participants will be recruited in the city library of Ghent (i.e. ‘De Krook’), in city halls and shopping malls. If a participant is willing to co-operate in the study, they will be offered a tablet and the pre-test measurement will take place. The participant will provide informed consent, choose a behaviour (PA or SB) and complete the questionnaires (see Fig. 3) via an online survey tool (https://www.limesurvey.org/) [72]. Subsequently, researchers will provide instructions on how to download the app. If the participant does not have sufficient time to fill out the questionnaire, they will receive a folder with a link and login code to start/complete the pre-test measurement at home. After completion of the pre-test measurement, the participant will be allocated to one of the eight groups, and will receive an email with the web-link to the appropriate version of the intervention. MyPlan 2.0 and its different conditions can only be accessed via the link sent by the researcher and, later on, via the provided email address of the participant. Participants have no access to the other experimental conditions of MyPlan 2.0. One week after each intervention session, an automatic email to encourage people to start with the following session will be sent. If participants take longer than expected to a complete session, several actions will be taken. Participants who do not start or complete a session after 1 week will be sent an email reminder. When there is no reaction after 2 weeks, participants will receive a telephone call from the researcher. When there is no reaction after 3 weeks, the participant will be considered as a drop-out.

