To evaluate the primary aim of the intervention, PA and SB will be analysed in one statistical analysis. The scores of PA and SB will be standardised (z-score) in order to obtain a common metric. For PA, the mean and SD of the population will be based on self-report IPAQ data self-report IPAQ data from Belgian adults (m_totalPA_ = 831.5 min/week, SD_totalPA_ = 579.8; m_MVPA_ = 459.9 min/week, SD_MVPA_ = 407.2 min/week) [77]. For SB, the mean and standard deviation of the population will be based on self-report SIT-Q-7d data from Belgian adults (m_totalSB_ = 9,57 h/day, SD_totalSB_ = 3,20 h/day) [78]. The z-scores for SB will be multiplied by − 1. That way the amount of healthy behaviour is reflected in positive scores. Mixed models (two levels: repeated measures clustered within participants) will be performed using the ‘lme4-package’ [79] to investigate the effect of the (combination) of the three behaviour-change techniques (i.e. action planning, coping planning and self-monitoring) on behaviour change [80]. The participants’ choice of target behaviour (i.e. PA or SB) will be included in the analysis as a moderator. Furthermore, to evaluate our secondary outcome, logistic regression analyses will be used to investigate whether the process on goal achievement has an influence on the primary outcome.

To evaluate the secondary aim of the intervention, PA and SB will be analysed both together for analysing the mediating effect of personal determinants. This because all participants filled out one version of the personal determinants (i.e. the version focussing on PA or the version focussing on SB). These outcome variables will be considered as personal determinants regarding the chosen health behaviour rather than personal determinants regarding increasing PA or decreasing SB. Mediating effects of the personal determinants of behaviour will be investigated using structural equation modelling [81]. Next, moderating effects of demographic variables will be identified via interaction terms by including them as an extra between factor in the analyses.

To evaluate the third aim of the intervention, three groups of participants will be identified based on their ‘mindset’ regarding behaviour change: ‘pre-intenders’, ‘intenders’ and ‘actors’. This will be based on their answer on the personal determinant ‘intention to change’. The moderating effect will be identified via interaction terms by also including them as an extra between factor in the analyses.

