## Discussion

There is a need for effective e- and m-health interventions that enhance behaviour change. Additionally, e- and m-health interventions need to be relevant, time-efficient and engaging. This study may contribute to a further understanding of how, why and for whom interventions work. By investigating the role of various behaviour-change techniques and determinants of behaviour change, we will be able to provide guidance for the development of future e- and m-health interventions. One of the strengths of this study is its experimental and longitudinal design, allowing us to isolate the effects of the separate behaviour-change techniques. To our knowledge, the influence of behaviour-change techniques has only been investigated as a combined effect or in a non-experimental way [53, 82, 83] and many authors in the field refer to the need for an experimental design [33–35]. Another strength of the study is the fact that not only PA and SB are measured via self-reports, but also a range of determinants is measured at different points in time, i.e. pre, post, at follow-up and during the intervention. This allows a thorough analysis of the processes of behaviour change that interventions can target. The results of such analysis can inform future interventions on how to tailor behaviour-change techniques to different participants in various phases of behaviour change. This study should provide a large and rich dataset to explore these research questions in detail. However, the study also has some limitations. First, PA and SB are measured by self-report questionnaires (IPAQ or SIT-Q-7d), which may lead to response and recall biases [84]. Future research may consider the use of objective measures of PA and SB. Second, to lower the burden for participants and thus preventing attrition, each determinant of behaviour change will be measured via only three items, which can compromise the reliability and validity of the measurement. However, the items that are included were iteratively constructed and validated by experts in health psychology. Third, the size of the groups will not allow us to draw conclusions about the three-way interactions. However, we are more interested in the main effects and the two-way interaction effects. Fourth, because participants can freely choose either to improve their PA or to reduce their SB, we cannot ensure that both versions of the programme will have the same number of participants. Lastly, due to attrition, it is possible that the sample size between groups will differ. Therefore, it will be important to focus on keeping the participants in the study via the use of email reminders and telephone calls.

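### The chosen behaviour is known before allocation and is the moderator in the primary model, but one unstratified list leaves group balance within each behaviour to chance: no bias, a small loss of precision, and a cheap remedy

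*Protocol article*

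**What the plan says.** The order of events is clear. The Intervention section states: "After behaviour selection, the allocation to one of the research groups takes place". Data collection procedures agrees. At the pre-test, "The participant will provide informed consent, choose a behaviour (PA or SB) and complete the questionnaires", and then "After completion of the pre-test measurement, the participant will be allocated to one of the eight groups".

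The Participants section describes the randomisation in some detail: "blocked randomisation will be used to form an allocation list for the eight different groups", using an online generator "with a block size of 40 will be used to assign the group numbers in random order within each block". When a pre-test is completed, "the participant will be allocated to the next number on the allocation list and will consequently be assigned to a group". The section gives 60 participants per group and mentions neither a stratification factor nor a separate list per behaviour.

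Data management and statistical analysis gives the choice a structural role in the primary analysis: participants' "choice of target behaviour (i.e. PA or SB) will be included in the analysis as a moderator". Among the limitations, the Discussion concedes that "we cannot ensure that both versions of the programme will have the same number of participants" and that attrition may make group sizes differ. It does not mention how the eight groups are spread within one behaviour.

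**The concern.** A factor that is recorded before allocation, decides which version of the programme a person receives and enters the primary model as moderator is a natural stratification factor. The list ignores it. Equal groups of 60 therefore hold overall but not within PA choosers or within SB choosers. Relative imbalance is largest in whichever behaviour fewer people choose.

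What is at stake is precision, in two places: technique effects estimated within the less popular behaviour, and the technique-by-choice terms, whose variance comes mainly from that behaviour. The PA:SB total cannot be controlled, as the Discussion says. The spread of the eight groups within each behaviour can be.

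**Working it through.** **Inputs from the protocol.** 480 recruited, eight groups, block size 40, 260 needed, 46% attrition accepted.

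**The plan's own figures.** 480/8 = 60 per group. 480/40 = 12 complete blocks, each with 40/8 = 5 per group. 1 − 260/480 = 45.8%, which agrees with 46%. All of these reproduce.

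**Assumed.** The share *p* choosing the less popular behaviour is not given, so it is varied from 10% to 50%. Attrition is taken as independent of group and behaviour.

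**Step 1: balance before attrition.** The list ignores the choice, so each group's count in the less popular behaviour is Binomial(60, *p*) with mean 60*p*. From 100,000 draws:

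| Share *p* | Mean per group | Median smallest to largest group | Chance that largest ≥ 1.5 × smallest |
|---|---|---|---|
| 50% | 30 | 25 to 35 | 38% |
| 40% | 24 | 19 to 29 | 65% |
| 30% | 18 | 13 to 23 | 85% |
| 20% | 12 | 8 to 16 | 96% |
| 10% | 6 | 3 to 9 | 99.6% |

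With separate lists in blocks of 40, the ranges become 30 to 30, 23 to 25, 16 to 20, 10 to 14 and 5 to 7. The remaining gaps come only from the last incomplete block.

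**Step 2: cost in variance after 46% attrition.** Let *X* be the design matrix in the less popular behaviour. The variance of a main effect is proportional to the matching diagonal element of (X′X)⁻¹. It is expressed relative to eight equal cells with the same total. Simulation, 4,000 runs, stratified lists in blocks of 8:

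| Share | Main effects only, unstratified v stratified | Reduction | With two-way terms, unstratified v stratified | Reduction |
|---|---|---|---|---|
| 50% | 1.018 v 1.011 | 1 − 1.011/1.018 = 0.7% | 1.037 v 1.023 | 1 − 1.023/1.037 = 1.4% |
| 30% | 1.035 v 1.019 | 1 − 1.019/1.035 = 1.5% | 1.077 v 1.042 | 1 − 1.042/1.077 = 3.2% |
| 20% | 1.056 v 1.031 | 1 − 1.031/1.056 = 2.4% | 1.145 v 1.071 | 1 − 1.071/1.145 = 6.5% |

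**Step 3: does the block size matter?** A separate run at 20% with two-way terms gave 1.142 unstratified, 1.076 with two lists in blocks of 40 and 1.073 with blocks of 8. Keeping 40 therefore gives 1 − 1.076/1.142 = 5.8%, nearly all of the gain.

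**Step 4: the technique-by-choice term.** Its variance is the sum of the variances in the two behaviours. With equal residual variance, the less popular one contributes (1/*p*) / (1/*p* + 1/(1 − *p*)) = 1 − *p*, or 80% at *p* = 20%. The gain for the interaction is therefore somewhat below the figures in Step 2.

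**Step 5: empty cells at a 10% share.** The chance that a given participant is both in the less popular behaviour and retained is 0.10 × 0.54 = 0.054. A group has no such participant with probability 0.946⁶⁰ = 0.036. At least one of eight groups is empty with probability 1 − 0.964⁸ ≈ 25%; simulation gave about 26%. With separate lists in blocks of 40 it was about 11%. At a 20% share the unstratified figure is only 0.8%.

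**Step 6: the effect pooled over PA and SB.** This compares 240 people with 240 (four groups of 60 on each side) under the existing list, whatever they chose. It is balanced already before attrition.

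**The case against.** The strongest reply is that nothing here is wrong. The blocked scheme is valid, it delivers 60 per group, allocation is random and the choice is in the model. Stratifying is then a preference worth a few per cent at most. Main effects pool four groups against four, so before attrition their efficiency within the less popular behaviour is still 99.1% at a 20% share and 98.1% at 10%. Most of the thinness of the cells comes from the small total and from attrition. At 20% the mean is 12 per group, about 6.5 after attrition, and the median smallest group is then 3 without stratification and 4 with it. All of this stands, and it sets the low priority.

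Predictability is the second reply. The researcher who allocates is unblinded after each assignment. With knowledge of past assignments, the best-guess rate is 24% with blocks of 40, 30% with 16 and 34% with 8. This is a good argument against small blocks. It does not count against two lists that keep blocks of 40.

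Two stronger readings are tempting. A reader might infer that the imbalance biases the primary result. The documents do not support that, because the imbalance is random and the choice is modelled. A reader might also average 1/n over all eight cells and obtain 1.18 v 1.09 at 20%, a gain of about 8%. That is the variance under a saturated model that includes the three-way interaction. The Discussion sets that interaction aside and names main and two-way effects as the interest. At 10% the same calculation can be finished only by discarding runs with an empty cell, so its ratio should not be relied on. One empty cell rules out the three-way term; seven cells can still support main and two-way effects, with poor precision.

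Finally, the article may condense a fuller protocol. But it specifies the generator, block size, list and drawing rule, and what it describes is a single list.

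**Conclusion.** The point holds as a minor design weakness. Choice precedes allocation and moderates the primary model, yet the described list does nothing to balance the eight groups within a behaviour. There is no bias, and technique effects pooled over PA and SB are hardly affected. The loss falls on behaviour-specific and technique-by-choice estimates. It is about 1% of variance at an even split, 1.5 to 3% at 30%, and 2 to 3% (main effects) to 6% (two-way terms) at 20%. Only a very uneven split, near 10%, makes empty cells a practical risk.

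These sizes rest on an assumed PA:SB split and on attrition of 46% that is unrelated to group or choice. Stratification would not cure a small total in the less popular behaviour or imbalance that arises from attrition.

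**What to change.** Generate two allocation lists with the same generator, one for PA choosers and one for SB choosers. Keep the block size of 40 in each. Draw the next number from the list that matches the choice recorded at the pre-test, and keep choice in the model as planned.

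The cost is one more list and a check of the recorded choice at each allocation, with no extra participants or visits. Exactly 60 per group becomes approximate, because each list may end in an incomplete block. Predictability within a list does not rise, since the block size is unchanged.

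Recruitment began in March 2018 and was due to end in April 2019. If it is still open, use the two lists for the remaining participants, record the date of the change and report it with the other protocol modifications. If it is too far advanced, report the group-by-behaviour counts at randomisation and at analysis, and add a sentence to the limitations in the Discussion.

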### Measurements

To answer our research questions, outcomes will be measured at five time points: 1 week before the intervention (PRE), immediately after session 1 (T1), immediately after session 3 (T2), maximum 1 week after the intervention (POST) and 1 month after the intervention (FU). Figure 3 shows which variables will be measured at each time point.

**Fig. 3 Fig3:**
[figure not shown]
Standard Protocol Items: Recommendations for Interventional Trials (SPIRIT) Figure. The figure shows the phases of the trial and the overview of variables measured at five time points

PA and SB, the primary outcomes, will be assessed via self-report measures. The IPAQ [61] will be used to measure self-reported total PA and moderate-to-vigorous PA across different domains (i.e. work, home, leisure time, transport). A 7-day sedentary behaviour self-report questionnaire (SIT-Q-7d) [62] will be used to measure domain-specific total sedentary time in five domains (meals, transportation, occupation, non-occupational screen time and other sedentary time). Both questionnaires have shown fair to good reliability and validity [61, 62]. Furthermore, users will report weekly to what extent they achieved their PA or SB goal (secondary outcome measure). After seeing the goal(s) they set the week before, the following question will be asked: ‘Did you reached your goal(s)?’: ‘Yes’, ‘No’ or ‘A little’.

To evaluate our second aim of the intervention, psychosocial determinants of behaviour (i.e. self-efficacy, motivation, outcome expectancies, risk perception, intention and the degree to which action planning, coping planning, self-monitoring is used in daily life) will be measured via a set of 32 items (i.e. at least three items per determinant). This set was iteratively developed and validated by an expert panel, using (1) cognitive interviewing [63, 64] and (2) a procedure for content validity which was based on the method of Johnston et al. (2014) [65]. In a first step a large pool of items were created measuring the personal determinants based upon the HAPA model [27]. Next, 11 experts in the field of self-regulation theory (which the determinants were based on) rated to what extent each item measured each construct of the HAPA model. Also feedback on the formulation was provided, and some items were reworded. Finally, a team of three researchers selected the best scoring items.

Participants will also complete questions regarding demographic information (age, sex, educational level, occupation, marital status, height and weight) and intervention usage (see ‘Process evaluation’). Furthermore, the short version of the ‘Instruments for Assessing Levels of Physical Activity and fitness’ (ALPHA) questionnaire [66] will be administered, which measures the perceptions of the physical environment (e.g. Are there many shops within easy walking distance of your home?). This questionnaire shows good reliability and predictive validity [66].

### Process evaluation

To gain insight in the different aspects of intervention integrity, we will conduct a process evaluation. Five components will be evaluated, based on the guidelines provided by Saunders, Evans and Joshi [67]: fidelity, dose delivered, dose received, recruitment and reach, and context.

#### Fidelity

Fidelity, also defined as quality, refers to the degree in which the intervention was carried out as planned. This will be assessed by rating the quality of the action and coping plans that participants create via the website and app. This will be done by scoring the plans both on instrumentality and specificity [68, 69].

#### Dose delivered

Dose delivered, or completeness, is the quantification of components of the website that were actually delivered in comparison to the components available. This will be measured by keeping track of the users’ website and app log data and counting how many online sessions they initiated and completed. We will keep track of how long users spend time on the website and app using the different components, how long it takes them to log back in and complete the intervention, how many times they have to be reminded for logging in again, if users complete optional components (such as the quizzes), and how many times they adapt their plan. Furthermore, at three different points in time (after session 3, post-intervention and follow-up intervention) users will rate how often they use the app (i.e. never, less than 1 day/week, 1 to 2 days/week, 3 to 4 days/week, 5 to 6 days/week, daily).

